### Outcome measurements

The participants answer a questionnaire on physical activity, health literacy, health-related quality of life and sociodemographic variables. The baseline questionnaire (T0) is answered at the beginning of the initial phase. The questionnaire at the end of the training phase (T1) and the 6 month follow-up questionnaire (T2) are collected using a postal questionnaire.

We chose leisure physical activity (MET^1^-min/week) as our primary outcome. Physical activity was operationalized by the Global Physical Activity Questionnaire [3, 24], which collects information on both physical activity during a typical week within three settings (workplace, transport and leisure time) as well as on sedentary behaviour. Activity specific scores are summed to give the total MET-min/week. Thereby, each minute of vigorous physical activity is multiplied by 8 METs and each minute of moderate physical activity by 4 METs. Bull et al. (2009) showed a moderate to strong positive relationship of the Global Physical Activity Questionnaire with the International Physical Activity Questionnaire (concurrent validity: Spearman’s rho 0.45–0.65), and the reliability was of moderate to substantial strength (kappa 0.67 to 0.73; Spearman’s rho 0.67 to 0.81) [3]. Compared to the accelerometer data, the Global Physical Activity Questionnaire provided low-to-moderate validity and generally acceptable evidence of reliability [25].

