### Further variables

For obtaining person-related variables, age, sex, height, weight, education level, family status and health-related lifestyle were assessed by unstandardized questions. Beyond, health-related Quality (HRQoL) of life was measured using the EQ-5D-5 l questionnaire [28]. The EQ-5D is a standardized measure of health status and assesses five dimensions of HRQoL: mobility, self-care, daily activities, pain and discomfort, anxiety or depression. EQ-5D-5 L provides five levels for answering each dimension: “no problems”, “slight problems”, “moderate problems”, “severe problems” and “extreme problems”. Descriptive answers were converted into a single summary index [29]. Index value of health status range from ‘1’ (perfect health) to ‘0’ (death). Beyond, workability was assessed by the work ability index (WAI) [30, 31] employability was measured by the 3-item subjective prognosis of gainful employment (SPE-scale) [32–34]. Overall, the following instruments are used (Table 2).

**Table 2 Tab2:** Summary of measures

	Instrument	Time of measurement^a^
Primary outcome measure		
Physical Activity	GPAQ Questionnaire ([3, 24])	T0, T1, T2
Secondary outcome measure		
Health literacy	Health literacy scale ([15])	T0, T1, T2
	HLQ Subscale „Actively managing my health“([27])	
Person-related variables		
Age, sex, height, weight,	Unstandardized questionnaire	T0
Education level, family status	Unstandardized questionnaire	T0
Health-related lifestyle	Unstandardized questionnaire	T0, T1, T2
Health Related Quality of Life	EQ-5D-5 L ([28])	T0, T1, T2
Work-related variables		
Workability	Work ability questionnaire ([30, 31])	T0, T1, T2
Employability	subjective prognosis of gainful employment (SPE-scale) (Mittag 2003 #57}; [33, 34])	T0, T1, T2

^a^ T0 = initial phase (baseline); T1 = End of training-phase; T2 = six month follow-up

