### Statistical analysis

Descriptive statistics will be used to describe the baseline characteristics of study population and to explore the distributions of the variables at the individual level. Depending on the distributions of the quantitative variables parametric and non-parametric tests are used to compare the intervention and the control group at baseline.

The two study groups will be compared using ANCOVA, with the outcome variables leisure time physical (primary outcome) activity and health literacy (secondary outcome), at 6 month follow-up set as the dependent variable [35]. Baseline values and the rehabilitation center will be used as a covariate to control for imbalance between control and intervention groups at baseline.

Standardized mean-difference effect size will be calculated by using the means of the two groups, mean-square error and the correlation between the covariate and dependent variable.

Intervention outcomes will be evaluated in relation to the base case data but also to the intention to treat principle. The base-case analysis will be performed using data restricted to those patients who replied to the postal 6 month follow-up questionnaire. The intention-to-treat analysis (ITT_LOCF_) will be performed assuming “last observation carried forward” since the effectiveness of physical activity promotion is considered controversial [36–38]: if 6 month follow-up data (T2) were missing, it was assumed that the physical activity data were the same as at baseline (T0). The statistical analyses will be conducted independently of the research team. The data will be analyzed using the statistical software IBM Statistics 23.0.

The calculated total sample size is 237 (ANCOVA: Fixed effects, main effects and interactions; Input: effect size f = 0.25 with 80 % power at p < 0.05; number of groups = 8 (group = 2; ambulatory rehabilitation center = 4); numerator df = 7; number of covariates = 2 (age; baseline value)). Therefore, it is estimated that a sample size of 119 participants per study arm would be required to detect a medium effect between the cross-provider intervention and the single-provider intervention. To allow for missing data and loss to follow up, we aim to recruit 150 participants per study arm.

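### The intention-to-treat rule is labelled LOCF but carries baseline (T0) forward, ignores T1, and can bias the arm difference if participants change from baseline

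*Protocol article*

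**What the plan says.** All of this is in the protocol article.

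- **Model.** Statistical analysis: ANCOVA comparing the two groups, with the outcome "at 6 month follow-up set as the dependent variable", adjusted for the baseline value and rehabilitation centre.
- **Two analyses.** Same section: "Intervention outcomes will be evaluated in relation to the base case data but also to the intention to treat principle".
- **Base case.** "The base-case analysis will be performed using data restricted to those patients who replied to the postal 6 month follow-up questionnaire".
- **Intention to treat.** It is labelled "last observation carried forward", with the reason "since the effectiveness of physical activity promotion is considered controversial". The rule is then spelled out: "if 6 month follow-up data (T2) were missing, it was assumed that the physical activity data were the same as at baseline (T0"). It is worded for physical activity only.
- **Measurements.** Outcome measurements: "The questionnaire at the end of the training phase (T1) and the 6 month follow-up questionnaire (T2) are collected using a postal questionnaire". Table 2, under Further variables, lists the physical activity questionnaire at T0, T1 and T2, with the note "T0 = initial phase (baseline); T1 = End of training-phase; T2 = six month follow-up".
- **Arms.** The cross-provider intervention and Quantitative study sections: both arms get the lifestyle programme (component A). Only the cross-provider arm is offered the coach (component B), including support between the end of training and the refresher day. Allocation follows the participant's health insurer and is not randomised.

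**The concern.** The label and the rule do not describe the same analysis. For a participant who answered T1 but not T2, the last observation is T1, yet the rule inserts T0. Two analysts, one following the name and one following the definition, would build different datasets for the primary outcome. The rule as defined also sets aside a measurement that the study collects.

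The reason given for the rule suits a different comparison. Assuming no change since baseline is cautious when an active programme is compared with nothing. Here both arms receive 16 weeks of training, so both may be more active at T2 than at T0. Setting non-responders back to T0 removes that gain from them, and removes more of it in the arm that loses more people. If retention differs between arms, part of the programme's shared effect can then appear as an effect of the coach, or hide one. Unequal retention is plausible because only one arm is offered coach contact in the months before the postal T2 questionnaire.

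**Working it through.** **The plan's own figure.** The sample size reproduces. Noncentral F with f = 0.25, numerator df 7, 8 groups and 2 covariates gives λ = 237 × 0.25² = 14.81, denominator df 237 − 8 − 2 = 227, and power 0.8004 at N = 237. Half of that is 118.5, rounded up to 119 per arm. Recruiting 150 implies an allowance of 1 − 119/150 = 20.7% loss. The article gives no loss by arm and no expected change from T0 to T2, so those values are assumed below.

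**Label against rule.**

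| Participant | Label (LOCF) uses | Rule uses |
|---|---|---|
| T0 and T1 answered, T2 missing | T1 | T0 |
| T0 only | T0 | T0 |

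The two agree only for people who answered neither postal questionnaire.

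**Expected bias.** Let g be the change from T0 to T2 common to both arms (in SD), d the coaching effect, and mI and mC the shares missing T2 in the cross-provider and control arms. Take missingness as random within arm and baseline means as equal. Imputed participants contribute zero change, so the expected arm difference is

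(1 − mI)(g + d) − (1 − mC)g

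and the bias is g(mC − mI) − d·mI.

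- With d = 0 the bias is g(mC − mI): 0.3 × 0.10 = 0.03 SD up to 0.5 × 0.20 = 0.10 SD. For a gain, it favours the better-retained arm.
- With g = 0 and d = 0 the bias is zero whatever the loss.
- With equal loss m the expected estimate is (1 − m)d, so 20% loss attenuates by 20%: 0.5 becomes 0.40.
- The two terms can cancel. With d = 0.5, mI = 0.15 and mC = 0.25, the bias is zero at g = 0.5 × 0.15/0.10 = 0.75.

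**Simulation check.** ANCOVA on arm and baseline, 150 per arm, correlation 0.5 between time points, 3000 runs, missingness random within arm. Centre was not modelled. d = 0.5 is the plan's f = 0.25 translated to two equal groups (d = 2f).

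| d | g | Missing T2, cross-provider / control | T0 carried forward: estimate, rejection | Responders only: estimate, rejection |
|---|---|---|---|---|
| 0 | 0 | 10% / 30% | 0.001, 5.3% | 0.002, 4.9% |
| 0 | 0.3 | 15% / 25% | 0.029, 5.9% | −0.003, 5.0% |
| 0 | 0.3 | 10% / 30% | 0.060, 9.9% | 0.000, 5.0% |
| 0 | 0.5 | 20% / 20% | −0.002, 4.5% | −0.001, 4.6% |
| 0 | 0.5 | 15% / 25% | 0.048, 8.0% | −0.002, 4.8% |
| 0 | 0.5 | 10% / 30% | 0.105, 20.0% | 0.006, 5.1% |
| 0 | 0.5 | 30% / 10% | −0.101, 19.3% | −0.001, 5.0% |
| 0.5 | 0.5 | 20% / 20% | 0.399, 98.2% | 0.498, 99.3% |
| 0.5 | 0.5 | 10% / 30% | 0.549, 100% | 0.498, 99.2% |
| 0.5 | 0.5 | 30% / 10% | 0.251, 69.8% | 0.500, 99.4% |

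With correlation 0.6, the 0.5 SD gain at 10% / 30% loss gives up to 21% rejection.

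**Carrying T1 forward instead.** This would match the label, but its null bias is (gain at T1 − gain at T2) × (mI − mC). If the gain falls from 0.8 SD at T1 to 0.3 SD at T2, then 10% / 30% loss gives 0.5 × (−0.20) = −0.10 SD. Simulated: −0.099, 15.4% rejection.

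**When responders only is not safe.** If control-arm reply also depends on T1 activity (assumed log-odds 0.8 per SD, retention 90% against about 72%, no true effect), responders only gives about −0.05 SD and 8% rejection, while T0 carried forward gives +0.10 SD and 21%. Both planned analyses leave T1 unused, and here they err in opposite directions.

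**The case against.** The strongest case on the other side is that the harm is conditional and that the plan already holds a sounder analysis.

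- **No universal bias.** A reader might infer that the estimate is biased whenever retention differs. It is not. With no mean change from baseline, or if non-responders really return to baseline, unequal loss does no harm of this kind. Small values do little: a 0.2 SD gain at 85% / 75% retention gives 5.2% rejection, and a 0.3 SD gain at 83% / 77% gives 5.3%. This stands.
- **Standard error.** A reader might infer that counting imputed values as observed makes the standard error too small. Under these assumptions it does not. The model standard error matched the sampling spread (0.0878 against 0.0875 at 80% / 80% retention; 0.0876 against 0.0871 at 90% / 70%). The excess rejections come from shifted means.
- **The other analysis.** A reader might infer that neither planned analysis can be relied on. The T0 rule does not touch the responder analysis, which is valid if reply depends only on arm and the model covariates.
- **Which analysis leads.** The responder analysis is called the base case and comes first, which fits intention to treat being the added analysis. A formal ranking may sit in the full plan. This softens the point, but the article's wording does not settle it.
- **Retention.** Coaching is optional, both arms have the refresher day, and T2 is postal for everyone. Unequal retention is plausible but not documented, and its direction is unknown.
- **Power.** At d = 0.5 and equal 20% loss, power stays at 98.2%. In that case the estimate suffers more than the test.

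None of this reconciles the label with the rule or makes the stated reason fit a comparison in which both arms are treated.

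**Conclusion.** The concern holds in a limited form. Two parts rest on the text alone: the rule contradicts its label, and it ignores T1 values that the study collects. A third follows by arithmetic: the rule is not reliably conservative for the coach contrast, because it can push the estimate in either direction and also attenuates a real effect under equal loss.

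The size is conditional. It needs a mean change from T0 to T2 and, for a false difference under no effect, unequal loss. The 0.03 to 0.10 SD and the 6 to 21% rejection rest on assumed gains of 0.3 to 0.5 SD, assumed retention gaps of 10 to 20 points around the implied 20.7% loss, missingness random within arm and equal baseline means. The attenuation, by contrast, needs only a real effect that non-responders share.

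The documents do not support calling the responder analysis unsound on account of this rule. Its own weakness is separate: it discards T1, which matters if reply depends on T1 activity.

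**What to change.** Replace the T0 rule as the intention-to-treat analysis. Analyse all allocated participants with T0 data, in the group to which they were allocated, using T0, T1 and T2 by one of two routes:

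- a mixed model for repeated measures with T1 and T2 as outcomes and baseline-by-time, group-by-time and centre terms, reading the effect at T2; or
- multiple imputation by arm from T0, T1 and baseline covariates, followed by the planned T2 ANCOVA with baseline and centre.

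Apply the same approach to health literacy, since the present rule covers physical activity only, and state that this analysis leads. Keep the responder analysis and the T0 rule as sensitivity analyses, the latter under the name baseline carried forward. Do not simply substitute T1 for T0, because that is biased if gains decay after training and loss differs by arm. Reporting T1 and T2 response by arm would show how much the choice matters.

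The cost is a change of wording and slightly more analysis work. T1 is already scheduled, so no new data are needed. The downside is reliance on missing at random given T0, T1 and the covariates, which the retained sensitivity analyses help to probe.

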### Qualitative study

The qualitative study comprises semi-structured interviews, systematic field notes of stakeholder meetings and document analyses. Semi-structured interviews and field notes will be conducted to explore the questions in regard to the RE-AIM dimensions i*mplementation* (“What are the facilitators and barriers for the cross-provider intervention?”; “Is the intervention conducted according to the manual?”; “What are the different stakeholders’ expectations and needs regarding health coaching in a work-related setting?”; “What are costs associated with implementation for the different stakeholders?”) and *maintenance* (“What structures resources were built in companies, providers and social insurers to implement the cross-provider intervention in daily routine?”) (see Table 1). The different stakeholders involved in the intervention (German Pension Fund Rhineland, cooperating statutory health insurers, providers, health-coaches, participants, company doctors and company management) will participate in the semi structured interviews.

In regard to health-coaching the semi-structured interviews encompass the perspectives of different stakeholders. Amongst others, the aim is to get information on tasks and objectives of health coaching, the necessary qualification, skills and competences of a health coach as well as the working methods and main topics in health coaching. The interview partners will be interviewed personally once, using semi-structured qualitative interviews. Two researchers lead through the semi-structured interviews: one will lead the conversation and the other one will do the documentation. If the participants agree, the interviews will be audio recorded. All semi-structured interviews will be in German. After the interviews are completed, transcriptions will be done according to the rules of Kuckartz [39]. Transcriptions will be double-checked.

The transcripts will be analysed according to the structuring content analysis by Mayring [40], which is similar to the framework approach [41]. For the analysis a qualitative research specialist at German Sport University Cologne, Germany will use the software MAXQDA 12 in order to code the information and look for relevant trends and themes within the data. Common themes and issues will be grouped together in main- and sub-categories and frequencies will be noted in order to highlight key issues. Though this is a qualitative study, the frequencies will be reported. However, direct quotations will be pulled from the session reports when they are illustrative of the issues. Overall, around 15 interviews will be included in this study, approximately two interviews per stakeholder group. Beyond, field notes of protocols of conversations with stakeholders (German Pension Fund Rhineland, statutory health insurances, health coaches, therapists and managers of ambulatory rehabilitation centers) and documents will be considered to gain insight into the dimension *adoption* (“How many providers offer the cross-provider intervention?”; “How many companies cooperate in the cross-provider intervention?”; “How many statutory social insurers cooperate in the cross-provider intervention?”) and i*mplementation* (“Is the intervention conducted according to the manual?”).

## Discussion

The study presented is designed to evaluate the effectiveness and the challenges of a workplace-related cross-provider intervention. Beyond, the expectations and needs on health coaching are of particular interest.

The study took as its starting point the new Preventive Health Care Act in Germany and its claim on cross-provider preventive measures [42, 43]. The second starting point of the study was significance and also the challenges of workplace-related health promotion. Despite the importance of workplace-related health promotion, the feasibility and the effectiveness are widely debated [24, 44]. On the one hand, the workplace is suitable reaching workers with health-risks for preventive measures [45–47]. On the other hand, participation rates in health promotion interventions at the workplace are low [25]. Overall, studies relating to workplace interventions are of high heterogeneity concerning interventions as well as population groups and therefore rarely comparable [48]. Nevertheless, study results support the superiority of multimodal interventions including ergonomic, behavior-related and workplace-related aspects compared to single interventions [49]. Workplace-related interventions should be multimodal and tailored to the needs and the preventive competence of both, the individuals and the organizations [50].

In regard to practical implications results may be relevant because of the clear orientation in employees with health-related risk factors. Since most studies focus mixed populations and do not differentiate interventions aiming at populations at risk and healthy persons [51] it is essential not only to develop but also to evaluate interventions with the ability to reach employees focusing on those who need it most [25, 51]. Hence, especially persons with health related risk factors (e.g. physical inactivity), people with a low socioeconomic status and men show a low rate of preventive activities [52, 53]. Beyond, the evaluation of the effectiveness of health coaching in regard to the sustainability of the preventive lifestyle measure is of high practical relevance. The study contributes to the professionalization in the field of health coaching not only by the evaluation of its effectiveness but also by the semi-structured interviews with different stakeholders providing a more profound understanding of the potential, challenges and qualification needs in health coaching.

There are several challenges in conducting this study. First, the present evaluation is performed in a real-life setting. This is a strength, on the one hand, because this provides a realistic estimate of effectiveness. On the other hand, several methodological challenges arise. Workplace-related interventions as well as studies promoting physical activity are fraught with methodological difficulties. Evidence development is considered a big challenge in prevention and health promotion [54–57]. Measures in health promotion are mainly complex interventions in complex socio-ecological systems [58] and several dimensions of complexity exist, for example the range of possible outcomes, the outcome variability in the target population and the number of elements in the intervention package itself [59]. Irrespective of the mode of intervention, evaluation of the impact therefore underlies high methodological standards and needs to consider three perspectives: multiplicity, context sensitivity and complexity as a reference point [56]. Although for many decades randomized controlled experiments have dominated the impact assessment of social or health programs, there are many arguments that stress the artificiality of these approaches as well as the lack of useful information produced [60, 61]. The World Health Organization even concluded that “the use of randomized control trials to evaluate health promotion initiatives is, in most cases, inappropriate, misleading and unnecessarily expensive” ([62], p. 5).

Realistic evaluation considers the complexity of health interventions and it may help to meet the challenges of evaluation in health promotion aiming at finding out how a program works, for whom and under what circumstances. The RE-AIM Framework provides a useful template to guide the design and implementation of a cross-provider intervention as it allows concurrent evaluation of dimensions considered relevant to ‘real world’ implementation.

The use of mixed methods within the research project enables a more complete picture of the intervention, its effectiveness and finding out how the intervention works, for whom and under what circumstances [63].
